## Abstract

**Background:**

Infection is the most important complication after acute stroke. This is substantially based on a stroke-induced immunosuppression. Heart rate variability (HRV) represents the autonomic nervous system activity in connection with stroke-induced immunomodulation and infections. We demonstrated in a feasibility study that HRV indices obtained in patients without acute post-stroke infections can predict infections in the subsequent sub-acute phase.

**Methods/Design:**

The study PRED-SEP is a prospective observational study. Adult patients with acute ischemic infarction in the territory of the middle cerebral artery and severe neurological deficit (National Institutes of Health Stroke Scale: NIHSS ≥ 8) are recruited. Primary endpoint is the development of infections, secondary endpoints are SIRS and severe sepsis in the sub-acute phase (day 3–5) after stroke and the functional outcome after 3 months. Infection is defined according to the PANTHERIS study and comprises pneumonia, urinary tract infection and infections without determined focus. SIRS and severe sepsis are defined according to German Sepsis Society guidelines. Functional outcome is measured by lethality and neurological scores (modified Rankin Scale, Barthel Index). Prognostic factors are HRV risk indices calculated from selected intervals of 24 h ECG measurements within 48 hours after symptom onset. It is planned to recruit 240 patients.

HRV risk indices (predictors) will be calculated according to standards and procedures previously developed and published by the authors. The predictive effects of HRV indices on infections will be estimated by fitting logistic regression models and estimating odds ratios with 95% confidence intervals. A prespecified modelling procedure will be applied to estimate unadjusted and confounder adjusted odds ratios. Secondary endpoints will be analysed in the same way. The functional outcome scales will be dichotomized. The association between HRV indices and pro- and anti-inflammatory markers will be quantified by calculating the appropriate correlation coefficients according to scale (Person or Spearman).

**Discussion:**

Since a general prophylactic antibiotic treatment after stroke is not recommended, results of this study could have essential implications for an early identification and hence, timely appropriate treating of stroke-induced infections.

**Trial registration:**

Prädiktoren für die Sepsis - Pred Sep, German Clinical Trials Register:
DRKS00003392.

## Background

Stroke-induced infection is the most relevant complication after acute ischemic stroke with further implications of developing severe sepsis and adverse outcome. Most relevant stroke-induced infections are pneumonia (4-22%) and urinary tract infections (UTI, 6.3-30.5%)
[1]). Both of which are associated with poor 3 months functional outcome (modified Rankin Scale score 3–6), namely pneumonia with OR = 4.4 (2.2-9.0) and UTI with OR = 2.7 (1.3-5.6)
[2]. In multivariate prediction models infection is an independent factor besides age and National Institutes of Health Stroke Scale (NIHSS) for 3 months functional outcome (modified Rankin Scale)
[3]. General antibiotic therapy in patients with acute stroke significantly reduced the incidence of infections, but only non-significantly reduced the number of patients who died
[4]. Preventive post-stroke antibiotic therapy is not recommended according to guidelines
[5]. Therefore, early antibiotic therapy is recommended as soon as an infection is identified
[6] and early markers of post-stroke infections are needed.

The analysis of the activity of the autonomous nervous system (ANS) may provide a novel timely appropriate approach for the early detection of developing infections. Stroke-induced immunosuppression mainly results from activation of sympathetic mediated pro-inflammatory cytokine production. In contrast, vagus nerve releases acetylcholine which inhibits the production of pro-inflammatory cytokines, but maintains production of anti-inflammatory cytokines
[7-10]. Those mechanisms are part of the “Central nervous system injury-induced immune deficiency syndrome” mediated by the sympathetic nervous system, the N. vagus (parasympathetic nervous system), and the hypothalamo–pituitary–adrenal (HPA) axis
[11]. After acute ischemic stroke overall heart rate variability (HRV) is depressed, while the sympathetic part dominates in connection with the reduced vagal HRV (e.g.
[12-14]).

In patients without any kind of brain damage HRV indices were correlated with inflammation markers. Higher levels of Interleukin 6 (IL-6) and C-reactive peptide (CRP) were typically associated with increased heart rate, reduced overall HRV, and reduced sympatho-vagal balance
[15-19]. In septic patients severity of illness was associated with reduced sympatho-vagal balance indices
[20]. Sepsis was predictable by reduced overall HRV
[21]. In patients with sepsis and multiple organ dysfunction syndrome reduced VLF (very low frequency power) was associated with a lower survival rate. In those patients the discriminatory value of altered sympatho-vagal control was strongest reflected by HRV complexity indices based on autonomic information flow (AIF)
[22-24].

In a feasibility study we enrolled prospectively forty-three patients with acute ischemic stroke. The predictability of sub-acute infections (day 4 ± 1 after admission) was investigated in 34 patients without acute infection by means of HRV indices obtained in the acute period (48 h after admission). Associations between HRV indices in the acute period and post-stroke infection in the sub-acute period were examined. Sub-acute infection could be predicted in patients without clinical or paraclinical (white blood cell count (WBC) and CRP) signs of infection in the acute period by: 1) an increased HFnorm (normalized high frequency power), but a reduced LFnorm (normalized low frequency power) as well as a reduced LF/HF ratio during the day for all parameters, and 2) a reduced LF (low frequency power) and VLF (very low frequency power) at night (all changes p < 0.05)
[25].

HRV indices are readily available from routine stroke monitoring systems. They were found to be associated with sub-acute post-stroke infections. Preceding the analysis of routine blood samples HRV analysis probably allows an early diagnosis of a developing infection. Thus, an HRV-based early diagnosis of post-stroke infection should be investigated in more detail. The method may have the potential of a novel tool to support decisions about a timely and appropriate treatment.

### Objectives

The primary objective of this study is the prediction of stroke-induced infections (primary endpoint) by means of HRV indices. Secondary endpoints are SIRS, severe sepsis, and functional outcome. In further analyses, correlations between HRV indices and blood markers will be explored and novel innovative HRV indices will be explored.

## Methods/Design

### Study design

The study is a prospective observational cohort study at the Hans Berger Department of Neurology, University Hospital Jena.

### Study population

*Inclusion criteria:*

– Patients with ischemic infarction in the territory of the middle cerebral artery with or without insular cortex involvement

– Age ≥ 18

– NIHSS ≥ 8

*Exclusion criteria:*

– Ongoing infections at admission

– History of previous strokes

– Cardiogenic arrhythmias

### HRV indices for prediction of outcomes

The key HRV risk indices are chosen according to the results of our feasibility study. HFnorm and LFnorm (markers of sympatho-vagal adjustment) are calculated from one defined 3 h interval during day time and VLF (integrative marker of autonomic and humoral control) is calculated from one defined 3 h interval during night time, both selected from the 24 h Holter ECG recordings that started within 24 h hours after onset of stroke symptoms.

### Outcome measures

*Primary endpoint:*

**Infection** defined according to the PANTHERIS study
[26]: I) pneumonia was defined as presence of at least one of the A and one of the B criteria: A) abnormal respiratory examination, pulmonary infiltrates in chest X-Ray; B) productive cough with purulent sputum, microbiological cultures from lower respiratory tract or blood cultures, leukocytosis, and elevation of CRP. II) Urinary tract infection was defined as the presence of two of the following criteria: fever (>38.0°C), urine sample positive for nitrite, leucocyturia, and significant bacteriuria. III) Infection was also diagnosed if temperature was above 38.0°C on at least 2 determinations with additional leucocytosis and positive blood cultures, but no determined focus.

*Secondary endpoints:*

– **SIRS:** criterium II according to Guidelines of the German Sepsis Society

– **Severe sepsis***:* criteria I, II and III according to Guidelines of the German Sepsis Society

– **Functional outcome**: day 5 and 3 months after insult (modified Rankin Scale, Barthel Index)

The cumulative incidence of infections, SIRS or severe sepsis will be estimated up to day 5 after the onset of stroke.

Guidelines of German Sepsis Society

I. **Confirmation of infection**

• Diagnosis of an infection on the basis of microbiological evidence or clinical criteria

II. **Systemic inflammatory host response (SIRS) (at least 2 criteria)**

• Fever (**≥**38°C) or hypothermia (**≤**36°C) confirmed by rectal, intravascular or intravesical measurement

• Tachycardia: heart rate **≥**90 bpm

• Tachypnea (frequency **≥**20/min) or hyperventilation (PCO2 **≤**4.3 kPa/ **≤**33 mmHg)

• Leukocytosis (**≥**12000/mm3) or leukopenia (**≤**4000/mm3) or **≥**10% immature neutrophils in differential blood count

III. **Acute organ dysfunction (at least 1 criterion)**

• Acute encephalopathy: reduced alertness, disorientation, agitation, delirium

• Relative or absolute thrombocytopenia: decrease in platelet counts by more than 30% within 24 hours or a platelet count of less than 100.000/mm3. Thrombocytopenia due to acute hemorrhage or immunological causes must be ruled out.

• Arterial hypoxemia: PaO2 **≤**10 kPa (**≤**75 mmHg) while breathing ambient air or a PaO2/FiO2 ratio of **≤**33 kPa (**≤**250 mmHg) on oxygen administration. A clinically manifest heart or lung disease must be ruled out as a cause of hypoxemia.

• Renal impairment: diuresis of **≤**0.5 ml/kg/h for at least 2 hours despite adequate volume resuscitation and/or an increase in serum creatinine level to > twice the upper limit of normal (ULN).

• Metabolic acidosis: Base excess of ≤ -5 mmol/L or lactate concentration of > 1.5×ULN.

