### Key data acquisition and individual time line

Patients are enrolled on day 1 after admission (at most 24 hours after symptom onset). The following baseline data are documented: demographic data, medical history, medications prior to admission, vital signs (including blood pressure, NIHSS), stroke characteristics such as symptom onset as well as ischemia location and size obtained by cranial MRI or CT, blood parameters (CRP, WBC) at admission to the emergency unit.

For the HRV analysis a 24 h-Holter-ECG recording is started on the morning after the stationary admission around 9 h00 (at most 24 h hours after symptom onset). A second 24 h-Holter-ECG is applied on day 5.

Up to day 5 the neurological status (NIHSS, Rankin Scale, Barthel-Index), clinical signs of infection (fever, pathological findings of examination) and blood parameters (CRP, WBC, PCT, cortisol, ACTH, copeptine, IL-6, IL-10, mHLA-DR, TNFalpha) are documented in a daily visit.

After 3 months patients are interviewed via by telephone contact to record the clinical outcome (Modified Rankin Scale, Barthel-Index).

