### Sample size

In a feasibility study 12 out of 34 patients (about 35%) with appropriate ischemic territorial stroke developed a new infection during day 3 to 5 after onset of stroke symptoms. Daytime LFnorm at baseline as a key HRV parameter was significantly lower in patients with infections compared to those without infections (mean = 40.1, SD = 19.4 and mean = 58.2, SD = 13.6, respectively). From the perspective of prognosis, an increase of LFnorm by one standard deviation (SD = 17.9) was associated with a 0.4 fold chance of getting an infection (OR = 0.4 or ln OR = β = -0.916). The logistic regression test of β =0 (α = 0.05 two-sided) will have 80% power to detect a β of -0.916 (OR = 0.4) with a sample size of 82 patients. To detect this effect while controlling for potential confounders sample size must be multiplied by the variance inflation factor 1/(1-σ^2^) where σ^2^ is the squared multiple correlation of LFnorm with further covariates in the model. A sample size of 136 will be necessary assuming σ^2^ = 0.4 and an infection proportion of 35% (nQuery Advisor 6.01).

According to the feasibility study 43% of patients had to be excluded after enrolment due to cardiogenic arrhythmias or ongoing infections at admission leaving about 57% of patients for the prognostic modelling. Therefore, a total of 240 patients should be allocated to the study.

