### Statistical analysis

HRV risk indices (predictors) will be calculated from selected intervals of 24 h ECG measurements according to standards and procedures previously developed and published by the applicant. The predictive effects of HRV indices on infections will be estimated by fitting logistic regression models and estimating odds ratios with 95% confidence intervals. A prespecified modelling procedure will be applied to estimate unadjusted and confounder adjusted odds ratios. Secondary endpoints will be analysed in the same way. The functional outcome scales will be dichotomized. The association between HPV indices and pro- and anti-inflammatory molecular markers will be quantified by calculating the appropriate correlation coefficients according to scale (Person or Spearman).

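### The SIRS endpoint has no at-risk condition, so SIRS already present at admission or during the Holter recording can count as an event predicted by HRV

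*Protocol article*

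**What the plan says.** All references are to the protocol article.

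- **Definition (Outcome measures).** SIRS is "criterium II according to Guidelines of the German Sepsis Society". Criterion II needs any two of four items: temperature, heart rate of 90 or more, respiration, and white cells. Infection is criterion I and is not required for SIRS.
- **Counting window.** Outcome measures states: "The cumulative incidence of infections, SIRS or severe sepsis will be estimated up to day 5 after the onset of stroke". The abstract (Methods/Design) says: "secondary endpoints are SIRS and severe sepsis in the sub-acute phase (day 3–5) after stroke".
- **Eligibility (Study population).** The exclusions are "Ongoing infections at admission", previous stroke and cardiogenic arrhythmia. None concerns SIRS without infection.
- **Model (Statistical analysis).** "Secondary endpoints will be analysed in the same way", that is, by logistic regression on the HRV indices, unadjusted and confounder-adjusted.
- **Timing of the predictor (Key data acquisition and individual time line).** The 24 h Holter starts on the morning after admission, at most 24 h after symptom onset. It therefore ends up to 48 h after onset.
- **Baseline data (same section).** Vital signs are recorded, and "blood parameters (CRP, WBC) at admission to the emergency unit".

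**The concern.** One population and one model serve infection, SIRS and severe sepsis, but the admission exclusion makes patients at risk at the start for only two of them. It covers infection directly, and severe sepsis through criterion I. A patient without infection who has a heart rate of 96 and a respiratory rate of 22 at admission is eligible and already meets the SIRS endpoint.

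The study aims to show that HRV in the acute period predicts what happens in the subsequent period. SIRS that overlaps the recording cannot support that aim. An association is also plausible without any prediction. Heart rate is a SIRS item, and the Background reports, in patients without brain damage, that higher inflammatory markers go with higher heart rate, reduced overall HRV and reduced sympatho-vagal balance. A cross-sectional link would then be reported as a prognostic odds ratio. Baseline SIRS is not among the confounders that Methods against bias gives as examples.

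**Working it through.** **1. The plan's own figures.** No figure is given for SIRS. The sample size for infection reproduces with the Whittemore–Hsieh formula for logistic regression on one continuous covariate, with P = 0.35 and β = −0.916 (β² = 0.839):

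- d = [1 + (1 + β²)·exp(5β²/4)] / [1 + exp(−β²/4)] = 3.451
- n = (1.960 + exp(−β²/4) × 0.842)² × (1 + 2Pd) / (Pβ²) = 81.2, so 82 as stated
- 81.2 / (1 − 0.4) = 135.3, so 136 as stated
- 136 / 0.57 = 238.6, so 239 against the stated 240

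These figures concern infection and are not in dispute. I use 136 below as the analysed number.

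**2. The rules side by side.**

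| Endpoint | Needs infection? | Excluded if present at admission? |
|---|---|---|
| Infection | yes | yes |
| Severe sepsis (criteria I, II and III) | yes | yes, through criterion I |
| SIRS (criterion II) | no | no |

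For infection, Sample size speaks of patients who "developed a new infection during day 3 to 5 after onset of stroke symptoms". No parallel wording exists for SIRS.

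**3. How many counted events could be carried over.** These rates are assumptions: SIRS at admission b = 10% to 30%, persistence to day 3–5 r = 30% to 70%, and new SIRS q = 15% to 25% of the rest.

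- Carried over = 136·b·r; new = 136·(1 − b)·q.
- Lowest share: 136 × 0.10 × 0.30 = 4.1 carried over and 136 × 0.90 × 0.25 = 30.6 new, giving 4.1/34.7 = 12%.
- Highest share: 136 × 0.30 × 0.70 = 28.6 carried over and 136 × 0.70 × 0.15 = 14.3 new, giving 28.6/42.9 = 67%.
- If counting runs from onset up to day 5, every patient with SIRS at admission counts: 13.6/(13.6 + 30.6) = 31% to 40.8/(40.8 + 14.3) = 74%.

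**4. Effect on the test.** Simulated trials of n = 136 with LFnorm standardised. An event is either new SIRS (25%, independent of LFnorm) or baseline SIRS that persists. Baseline SIRS depends on LFnorm through the stated odds ratio (OR) per SD. The slope is tested unadjusted at a nominal 5%. LFnorm predicts no new SIRS in this set-up, so a valid test of prediction would reject in 5%.

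| Persistence | Baseline OR per SD | Rejection at baseline SIRS 10% / 20% / 30% |
|---|---|---|
| 80% | 0.5 | 14% / 31% / 46% |
| 50% | 0.5 | 10% / 15% / 20% |
| 30% | 0.5 | 5% / 8% / 11% |
| 80% | 0.8 | 5% / 7% / 10% |
| 50% | 0.8 | 6% / 5% / 7% |

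With 2,000 trials per cell the simulation error is at most about √(0.46 × 0.54/2000) = 1.1 percentage points. If every baseline case counts (OR 0.5), as the up-to-day-5 wording allows, the rates are 18%, 44% and 64%. Adjustment reduces precision: at an effective n of about 136 × 0.6 = 82, the first row falls to 11%, 18% and 30%.

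**The case against.** **Cumulative incidence already means new cases.** That is the usual meaning and may well be intended. It does show that the text cannot be taken as proof that prevalent SIRS will be counted. But no stated criterion turns the term into a rule for SIRS, and counting up to day 5 from onset includes the admission period.

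**The day 3–5 window takes care of it.** Only in part. It removes SIRS that has resolved by then, but not SIRS that persists.

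**The analysis plan or study manual may define the risk set.** It may; neither is shown. This point therefore concerns what the article fixes: the endpoint definition, the exclusions, the window and the instruction to analyse SIRS like infection. Taken together, these do not give an incident endpoint.

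**The size rests on assumptions.** This stands. A reader might infer from the top of the range that the SIRS analysis is bound to yield a false positive. The documents give no SIRS prevalence, persistence or HRV association, and with low persistence or a weak baseline association the inflation is negligible.

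**Other stronger readings.** A reader might infer that the primary endpoint or the sample size is compromised; neither is, since infection at admission is excluded and 240 was derived for infection. A reader might also argue that SIRS should have to be confirmed on two consecutive visits. The article adopts a guideline definition without such a rule, and day-to-day variation unrelated to HRV would dilute an association rather than create a spurious one.

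**Conclusion.** The point holds on the text. As stated, the rules let SIRS that is present at admission, or that arises before or during the HRV recording, count as an event predicted by HRV. What is shown is a gap in the endpoint rules, not that the investigators will count such cases.

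The consequence ranges from negligible (about 5% rejection) to large (about 46%) for an unadjusted test at n = 136, within the assumed ranges: baseline SIRS 10% to 30%, persistence 30% to 80%, baseline OR 0.8 to 0.5 per SD, and new SIRS 25% unrelated to HRV. One secondary endpoint is affected. Because the correction is cheap and the size cannot be bounded from the documents, it should be made before the data are analysed.

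**What to change.** For the SIRS model only:

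1. Restrict the risk set to patients who do not meet criterion II at admission or at any daily visit up to the end of the HRV recording. A check at admission alone is not enough, because the Holter starts the next morning.
2. Count only SIRS newly met after the recording ends, within the day 3–5 window of the abstract, and bring the up-to-day-5 sentence in Outcome measures into line for this endpoint.
3. Report the number of patients with earlier SIRS, and label any HRV association in them as cross-sectional.

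The vital signs and white cell count already documented should serve. The article does not name respiratory rate, temperature or PCO2 among the baseline vital signs, so confirm in the study manual that the criterion II items are recorded from admission on; the endpoint itself needs the same items on later days. The cost is analysis-plan wording and fewer patients and events in one secondary analysis.

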## Discussion

The goal of this study is to show that HRV indices obtained in the acute post-stroke period are able to predict infections in the subsequent sub-acute period. HRV indices represent the role of ANS activity in connection with immunomodulation and developing infections after stroke. They would be readily available from routine ECG stroke monitoring systems. Their continuous consideration would allow an earlier identification and, hence, timely appropriate treatment of developing infections.

Recently, the clinical A^2^DS^2^ score to predict pneumonia in acute ischemic stroke was developed and validated using data of two independent stroke registers. This 10-point risk score (points) includes age ≥75 years (1), atrial fibrillation (1), dysphagia (2), male sex (1), stroke severity according to the National Institute of Health Stroke Scale 0–4 (0), 5–15 (3), ≥16 (5)
[29].

Biomarkers obtained from post-stroke blood samples, like WBC, CRP, PCT, and copeptin were all independent predictors of pneumonia, UTI, and other infections
[30]. Those authors concluded that “the combination of established inflammatory makers (WBC, CRP) combined with a biomarker of stress (copeptin) or a biomarker of bacterial infection (PCT) probably reflects better the complexity of an infection than one biomarker alone and may lead to a more accurate prediction of a beginning but not yet clinically apparent infection”.

In addition to the HRV indices all components of the A^2^DS^2^-score and the above mentioned blood markers are recorded in our study. We will be able to put our HRV study results into perspective by analysing several potential predictors and, depending on the number of observed outcome events, their combinations in multiple regression models.

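### The endpoint window is stated in conflicting ways; the version in Outcome measures would count infections that arise before or during the HRV recording as predicted events

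*Protocol article*

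**What the plan says.** The protocol article describes the time window of the endpoints in four places.

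- **Outcome measures:** "The cumulative incidence of infections, SIRS or severe sepsis will be estimated up to day 5 after the onset of stroke". This has an upper limit and no lower one, and it covers infection, SIRS and severe sepsis alike.
- **Abstract, Methods/Design:** "Primary endpoint is the development of infections, secondary endpoints are SIRS and severe sepsis in the sub-acute phase (day 3–5) after stroke".
- **Sample size:** 12 of 34 feasibility patients "developed a new infection during day 3 to 5 after onset of stroke symptoms". The 35% event rate is built on this.
- **Discussion:** the goal is to show that "HRV indices obtained in the acute post-stroke period are able to predict infections in the subsequent sub-acute period".

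On the predictor, HRV indices for prediction of outcomes takes one 3 h daytime and one 3 h night-time interval from "24 h Holter ECG recordings that started within 24 h hours after onset of stroke symptoms". The abstract puts these intervals within 48 hours of symptom onset.

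On who is at risk, the only exclusion for early infection in Study population is "Ongoing infections at admission". No criterion concerns SIRS at baseline. For the feasibility study, the Background says that prediction "was investigated in 34 patients without acute infection by means of HRV indices obtained in the acute period (48 h after admission").

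**The concern.** The study's claim is about order in time: HRV changes first, infection follows. That needs patients who are free of infection when HRV is measured, and events that start afterwards. The Outcome measures sentence secures neither. A patient who is clean at admission, becomes infected on the first or second day and has the Holter running at that time would enter the logistic model as an event, with a predictor measured during or after the infection.

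The Background supplies a mechanism. In patients without brain damage it links higher IL-6 and CRP with faster heart rate, lower overall HRV and reduced sympatho-vagal balance. The feasibility predictors of infection include lower LFnorm and a lower LF/HF ratio. An infection already under way could therefore produce the hypothesised association even if HRV had no predictive value. Calculating HRV blinded to outcome does not prevent this.

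SIRS is more exposed. A heart rate of 90 bpm or more is one of its criteria, and a patient who meets SIRS at admission is not excluded.

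**Working it through.** **1. The windows side by side**

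| Item | Earliest | Latest | Section |
|---|---|---|---|
| Infection exclusion | admission | admission | Study population |
| First Holter | starts at most 24 h after onset | at most 24 + 24 = 48 h after onset | HRV indices; Key data acquisition; abstract |
| Events, version A | not stated | day 5 | Outcome measures |
| Events, version B | day 3 | day 5 | Abstract; Sample size |
| Events, version C | after the acute period | sub-acute period | Discussion |

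Under version A, the interval from admission to the end of the recording lies inside both the event window and the measurement window, and no rule covers it. Under version B the event window starts once the first 48 h are over, but patients infected in that gap still have no stated status.

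**2. The plan's own sample size**

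Inputs from Sample size: p = 0.35, β = 0.916 in absolute value, two-sided α = 0.05, power 80%, squared multiple correlation 0.4, retention 57%. The 1989 Hsieh formula for one continuous covariate is

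n = [z(0.975) + z(0.80)·exp(−β²/4)]² · (1 + 2pδ) / (pβ²), with δ = [1 + (1 + β²)·exp(5β²/4)] / [1 + exp(−β²/4)].

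Here exp(−β²/4) = 0.811 and δ = 3.45.

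- n = 81.2, stated as 82.
- 81.2/(1 − 0.4) = 135.3, stated as 136.
- 136/0.57 = 238.6, stated as 240.

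The figures reproduce. They rest on a day 3 to 5 event rate, so they match version B and not version A.

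**3. What early events could do (illustration)**

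Assumed: 136 patients, 35% with an event, no relation between LFnorm and later infection, and a share q of events that are early, with LFnorm lowered by d SD. The model is an unadjusted logistic regression with a Wald test at 5%.

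| q | d | OR per SD | False-positive rate |
|---|---|---|---|
| 10% | 0.5 | 0.95 | 6% |
| 10% | 1 | 0.90 | 8% |
| 25% | 0.5 | 0.88 | 10% |
| 25% | 1 | 0.78 | 26% |
| 43% | 0.5 | 0.81 | 21% |
| 43% | 1 | 0.65 | about 60% |

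The documents give neither q nor d. The 1 SD value borrows the feasibility difference between later-infected and uninfected patients: 58.2 − 40.1 = 18.1, against an SD of 17.9. The 43% is 9/(9 + 12), where 9 = 43 − 34 feasibility patients were not in the infection-free set. It would apply only if all nine became infected after admission, which the documents do not say. It is unrelated to the 43% post-enrolment exclusion in Sample size.

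**4. What a landmark could cost**

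Same formula solved for power, with p = 0.35 and β = 0.916 held fixed:

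- 136 evaluable: 80%.
- 122 evaluable (10% lost, 136 × 0.90): 75%.
- 108 evaluable (136 × 34/43, as if all nine were post-admission infections): 69%.

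**The case against.** The strongest reply is that the window up to day 5 is not the settled endpoint. The sentence in Outcome measures gives an upper limit and does not say that counting starts at stroke onset. It can also be read as a descriptive estimate, since Statistical analysis does not repeat it for the logistic models. The other statements favour the later window. This stands: the defect is a contradiction, not a fixed wrong endpoint. The abstract is not decisive, however, because its day 3 to 5 phrase may grammatically attach only to SIRS and severe sepsis.

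Second, the exposed interval is limited. Infections at admission are excluded, the predictors use two 3 h intervals rather than the whole recording, and 48 h is a maximum. This also stands. Not every infection before hour 48 overlaps the measurement.

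Third, a reader might infer that the feasibility study removed exactly the patients infected between admission and 48 h, so that up to 43% of events here would be early. The documents do not support that. The Background speaks of no infection in the acute period, but Sample size attributes the feasibility exclusions to arrhythmias or infections ongoing at admission. None of the nine is shown to have been infected after admission.

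Fourth, the analysis plan and study manual, which are not shown, may define the at-risk set. They may, but that would not reconcile the conflicting statements in this document.

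**Conclusion.** The point holds as a contradiction that should be fixed. Outcome measures sets no lower bound, while the abstract, Sample size and Discussion point to a later window. No stated rule deals with patients who become infected between admission and the end of the first Holter. If the Outcome measures sentence is followed as written, some counted events can precede or overlap the predictor measurement. SIRS present at baseline can be counted as well.

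The size of the bias in this study is unknown. The illustrative range (odds ratio about 0.95 to 0.65, false positives about 6% to 60%) rests on assumed early shares and assumed LFnorm shifts, and its upper end combines the two most extreme inputs. It shows that the mechanism can matter, not that the study's result would be spurious. If days 3 to 5 are intended and applied, the problem is smaller, but the wording and the at-risk set still need correcting.

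**What to change.** Replace the counting sentence in Outcome measures with a landmark definition:

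- **Analysis set:** patients free of infection at the end of the first Holter recording.
- **Primary event:** first infection on days 3 to 5 after onset.
- **Earlier infections:** listed separately and not counted as events.
- **SIRS and severe sepsis:** same landmark. Patients who already meet SIRS at the landmark leave the SIRS analysis.

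Use the same window in the abstract, Sample size and Discussion.

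No new data are needed in principle, because the daily visits to day 5 already record clinical signs of infection, CRP and WBC. The cost is precision. Patients infected between admission and the landmark leave the primary analysis, and the 57% retention in Sample size is attributed to arrhythmias and infections at admission, so it does not clearly allow for them. If few are lost, and the 35% is a day 3 to 5 rate as stated, 82, 136 and 240 stand. If they are numerous, the 80% power should be restated, with the 75% and 69% above as examples.
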